#### Acceptability and experience of outpatient IOL

Further, outcomes relating to the acceptability and experience of the woman, her partner and the care providers will be studied:

Questionnaires measuring general self-efficacy (GSE),^32^ health-related quality of life (HRQL) (EuroQol Visual Analogue Scale (EQ-VAS) and EuroQol 5-Dimension (EQ-5D)),^33 34^ sense of coherence (SOC-13),^35^ pain catastrophising (PCS)^36^ and depression (The Edinburgh Postnatal Depression Scale, EPDS)^37^ at baseline are sent out by email and/or short message service (SMS) to women and partners after inclusion, but before randomisation. Three months after delivery, the GSE, EQ-VAS, EQ-5D, SOC, PCS, EPDS, childbirth experience questionnaire (CEQ2),^38^ father for the first-time questionnaire (FTFQ)^39^ and Breastfeeding Self-Efficacy Scale Short Form (BES-SF)^40^ are distributed by email and/or SMS. Furthermore, the experience of IOL will be evaluated by a questionnaire adapted from Bollapragada *et al*,^41^ allowing participants to provide free-text responses. Partners at one centre are invited to a web-based qualitative questionnaire adapted from Daniels *et al*^42^ 3 months after delivery. In all participating partners, background characteristics (age, education level, number of children and number of experienced childbirths and IOL) are registered. All questionnaires are validated in Swedish and English.

In addition to the questionnaires, a qualitative approach will involve interviewing 15–20 women and 15–20 partners 3–6 months after delivery. These informants will be strategically selected from diverse age groups, parity and socioeconomic backgrounds to ensure a comprehensive spectrum of experiences of the phenomenon (outpatient) IOL. Care providers consisting of 15–20 individuals will also be strategically selected based on various criteria including age, gender, profession (midwife, physician, assistant nurse), workplace and specific tasks, such as answering phone calls, working at the induction unit, delivery unit or postnatal care unit. Focus group or individual interviews will be conducted in Swedish or English at the hospital, in the woman’s/partner’s/healthcare provider’s home or via digital meeting options, depending on their preference. An open-ended question will be used: “Please tell me of your experience of (outpatient) induction”. Follow-up questions, such as “How did that feel” and “Can you please tell me more,” will also be asked to deepen understanding. The interviewer will create an open climate to enable the informant to find the right words to express her/his experiences.^43^ Interviews will be audiotaped and transcribed verbatim.

#### Health economic outcome

The following variables will be included in the health economic analyses: pregnancy, child and maternal outcomes including time from start of IOL to delivery (source: SPR, eCRF), time in the hospital prior to and after delivery (any ward) (source: SPR, eCRF), number of calls for counselling and visits to the hospital after start of IOL including reasons for these visits and phone calls (source: eCRF). Mode of delivery; spontaneous vaginal birth, instrumental vaginal birth or caesarean section (source: SPR), time from IOL to active labour (source: SPR), primary method of IOL (source: SPR), additional methods of cervical ripening prior to amniotomy (source: SPR, eCRF), duration of stay at hospital after delivery (source: SPR), unscheduled visits postpartum (source: SPR, patient chart, the National Patient Register), readmission postpartum within the first month (source: SPR, patient chart, the National Patient Register).

#### Future pregnancy outcomes

The number of future deliveries, start and mode of delivery, fear of childbirth and patient satisfaction with future births will be followed through the SPR 10 years after delivery.

### Power calculation

Non-inferiority will be tested with a two-sided 95% CI and 80% power. Calculating with 2.8% (based on data from the SPR 2014–2018^5^) for the primary composite outcome in outpatients and 2.3% in inpatients and a 5% drop-out rate, 8891 women need to be randomised to achieve a probability ≥0.80 that the upper limit of a two-sided 95.7% CI for the difference in primary outcome will be less than the non-inferiority margin 1.5%. The vaginal delivery rate was 88% in a group of women fulfilling the eligibility criteria (SPR, 2014–2018^5^). Assuming a vaginal delivery rate of 90% in the outpatient arm, calculating with 80% power, a two-sided 99.3% CI, a non-inferiority margin of 1.5% and a 5% drop-out rate, 2119 women need to be randomised to each arm induced with either balloon catheter or oral misoprostol to assess efficacy of either method in the different IOL settings.

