**Method and analysis:**

A register-based randomised controlled multicentre non-inferiority trial to study if outpatient induction in low-risk inductions is (1) as safe for the child (perinatal composite of mortality and morbidity) and (2) as effective (proportion of vaginal deliveries) as inpatient induction at the hospital. Secondary outcomes are further health outcomes, experiences of pregnant women, partners and care providers, health economics and future pregnancy outcome. Participating women with a singleton pregnancy and unripe cervix between 37+0 and 41+6 gestational weeks planned for low-risk induction will undergo induction of labour with either a balloon catheter or oral misoprostol according to clinical practice at the study site and the woman’s informed choice. Randomisation will allocate women to either outpatient (home or patient hotel) or inpatient induction (standard care). Women undergoing outpatient induction can remain at home for up to 2 days, with an assessment after 24 hours including cardiotocography. Once active labour ensues, all women will receive standard care in the hospital.

The assessment of non-inferiority will involve a two-sided 95% CI and 80% power, requiring randomisation of 8891 women to ensure a probability of at least 0.80 that the upper limit of a two-sided 95.7% CI for a difference in the primary safety outcome is below the non-inferiority margin of 1.5%. 31 of the 45 delivery units in Sweden are currently recruiting. Data will be collected from the electronic case report form and Swedish healthcare registers. Questionnaire and qualitative interview-based studies will be performed to explore experiences of pregnant women, partners and care providers. Additionally, a health economic evaluation will be performed.

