#### Data analyses

The final statistical analysis plan (SAP) will be set prior to data lock. All main analyses will be performed according to ITT, and complementary analyses will be performed on the per-protocol population. The statistician performing the analyses will be blinded to allocation and primary IOL method.

For comparison between the two allocation groups, Fisher’s exact test will be used for dichotomous variables, Fisher’s non-parametric permutation test for continuous variables, Mantel-Haenszel χ² test for ordered categorical variables and Pearson’s χ² test for non-ordered categorical variables. For all comparisons between the two groups, regarding dichotomous and continuous variables, mean differences with 95% CI will be calculated.

For the primary outcome variable and other dichotomous outcome variables, multivariable binary regression will be used for the adjustment. For continuous variables, analysis of covariance (ANCOVA) will be used for the adjustment.

For dichotomous variables, risk difference with 95% CI and risk ratio with 95% CI will be calculated between the two groups and 95% CIs for the estimated proportions. The distribution of continuous variables as well as change in continuous variables will be given as mean, SD, median, minimum, maximum, and first and third quartiles. Categorical variables will be given as number and proportion. Exploratory analyses will be performed on subgroups stratified for parity (primiparous vs multiparous women), initial method of IOL (balloon catheter vs oral misoprostol), Bishop score in women without PROM (<3 versus ≥3), indication for IOL (PROM vs other than PROM) and reported travel time to the hospital (<30 min and ≥30 min).

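### The article says non-inferiority is tested with a 95% CI, but it sizes safety on 95.7% and efficacy on 99.3% and never states how these levels relate

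*Protocol article*

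**What the plan says.** The article defines two primary outcomes (Outcomes, Primary outcomes): a perinatal safety composite and the proportion of vaginal deliveries. Four statements bear on the confidence level.

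- **Power calculation, opening sentence**, with no outcome singled out: "Non-inferiority will be tested with a two-sided 95% CI and 80% power".
- **Power calculation, safety.** The size is chosen so that, with probability at least 0.80, "the upper limit of a two-sided 95.7% CI for the difference in primary outcome will be less than the non-inferiority margin 1.5" (percentage points).
- **Power calculation, efficacy.** The size is obtained "calculating with 80% power, a two-sided 99.3% CI, a non-inferiority margin of 1.5% and a 5% drop-out rate".
- **Abstract, Method and analysis.** One sentence holds both "The assessment of non-inferiority will involve a two-sided 95% CI and 80% power" and the requirement that "the upper limit of a two-sided 95.7% CI for a difference in the primary safety outcome is below the non-inferiority margin of 1.5" (percentage points). It does not mention 99.3%.

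The Data analyses section describes estimates for dichotomous variables in general: "risk difference with 95% CI and risk ratio with 95% CI will be calculated between the two groups". Neither 95.7% nor 99.3% appears there. The same section says the final SAP is still to be set before data lock.

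Nowhere does the article call 95% an overall level, explain where 95.7% and 99.3% come from, or say whether a non-inferiority claim needs both primary outcomes or only one.

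**The concern.** A non-inferiority conclusion depends on where one confidence limit falls relative to a margin, so the level of that interval is the decision rule. Here the general sentence gives one level and the outcome-specific sentences give two others. A safety result whose 95% CI lies below 1.5 points while its 95.7% CI does not could be read either way, with a sentence in the article to support each reading.

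The gap is wider for efficacy, where 95% and 99.3% are far apart. If the opening sentence were applied to both outcomes, and each could be claimed separately, the trial would run at a higher familywise error than the one it appears to have been designed for. Treatment is not blinded and the outcome is perinatal death and morbidity, so the rule should be unambiguous before the data are seen.

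**Working it through.** **Inputs (Power calculation; allocation from Randomisation).**
- Safety: 2.8% outpatient, 2.3% inpatient, margin 1.5 points, 80% power.
- Efficacy: 90% vaginal delivery outpatient, 88% inpatient, margin 1.5 points, 80% power. In terms of caesarean section this is 10% against 12%.
- Drop-out 5%, applied as division by 0.95. Allocation 1:1.
- Alpha is 1 minus the confidence level: 0.043 for 95.7%, 0.007 for 99.3%, 0.05 for 95%.

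**Formula (Farrington-Manning).** n per arm = [(z(1−α/2)·s0 + z(0.80)·s1) / (margin − true difference)]². Here s1 uses the assumed rates, s0 uses the rates restricted to the margin, and z(0.80) = 0.8416.

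**Reproducing the safety size.**
- s1 = √(0.028×0.972 + 0.023×0.977) = 0.22291. The restricted rates are 3.436% and 1.936%, so s0 = 0.22840. The denominator is 0.015 − 0.005 = 0.010.
- At 95.7% (z = 2.0237): n = 4,222.6, so 4,223 per arm. 2 × 4,223 / 0.95 = 8,890.5, so **8,891**, as published.
- At 95% (z = 1.9600): n = 4,035.5, so 4,036 per arm. 2 × 4,036 / 0.95 = 8,496.8, so 8,497.

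**Reproducing the efficacy size.**
- s1 = √(0.10×0.90 + 0.12×0.88) = 0.44227. The restricted rates are 11.854% and 10.354%, so s0 = 0.44418. The denominator is 0.015 + 0.020 = 0.035.
- At 99.3% (z = 2.6968): n = 2,012.5, so 2,013. 2,013 / 0.95 = 2,118.9, so **2,119**, as published.
- At 95%: n = 1,260.9, so 1,261. 1,261 / 0.95 = 1,327.4, so 1,328.

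**Sensitivity to the formula.** For safety at 95%, an unpooled Wald formula gives 8,211 and a continuity-corrected one 8,628, so neither reaches 8,891. At 95.7% they give 8,590 and 9,007, on either side of it. For efficacy, Wald gives 1,320 at 95% and 2,106 at 99.3%. The conclusion about the design levels does not depend on the choice of formula.

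**What the levels add up to.**
- Two-sided: 0.043 + 0.007 = 0.050. One-sided: 0.0215 + 0.0035 = 0.025.
- If 95% decides both outcomes and either can be claimed, the one-sided bound is 0.025 + 0.025 = 0.050. If the outcomes are independent it is 1 − 0.975² = 0.0494.
- Efficacy alone goes from 0.0035 to 0.025 one-sided, a factor of about 7.

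**A further ambiguity in the split.** The power section links the 2,119 per arm to assessing each induction method. If balloon and misoprostol are each tested at 99.3%, the sum is 0.043 + 0.007 + 0.007 = 0.057 two-sided, and the split no longer adds to 0.05.

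**The case against.** The strongest reply is that 95% is simply the overall level and the other two are the per-outcome levels. The exact sum of 0.05 supports this, and the abstract, with 95% and 95.7% in one sentence, can be read that way. It is probably what was meant. But the opening sentence gives 95% as the level of the interval used for testing, and nothing labels it as overall. What remains is an unlabelled and contradictory level that one sentence can repair.

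Three stronger readings are tempting, and the article does not support them.

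- *Error control is already lost.* That requires 95% to decide both outcomes despite the explicit 95.7% and 99.3%, and either outcome to be claimable alone. The objective names safety and efficacy together. If both had to be met, 95% for each would inflate nothing. The article does not settle this, although a requirement for both would leave the split levels unexplained.
- *The Data analyses section prescribes a competing decision interval.* Its 95% CIs are general reporting for all dichotomous variables, and it mentions neither the margin nor non-inferiority. It is a place to align, not a second contradiction.
- *The split wastes alpha because nothing is passed on once one outcome succeeds.* A plain Bonferroni split is valid, and recycling is a preference. Under the article's own 90% against 88%, a pooled efficacy test with 4,223 analysed per arm already has 99.3% power at the 99.3% level (Wald), so recycling would gain almost nothing there. A two-test recycling rule would also not cover separate tests by induction method.

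Leaving the matter to the SAP is a fair answer to an omission. It does not answer levels that the article itself states inconsistently.

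**Conclusion.** The point holds as an inconsistency in the stated decision level. The general 95% sentence in the abstract and the power section conflicts with the 95.7% and 99.3% on which the trial was sized, and the exact reproduction of 8,891 and 2,119 leaves little doubt which levels were designed. That 0.05 was divided as 0.043 + 0.007 is an inference from those levels, since the article does not say it.

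The consequence is conditional: a rise in the one-sided familywise bound from 2.5% to at most 5%, and in the efficacy test from 0.35% to 2.5%, if 95% decides both outcomes and either can be claimed alone. A reader might infer that the trial is wrongly sized. It is not: with 8,446 evaluable women the Wald power for safety is 81.4% at 95.7% and 83.0% at 95%. Only the wording of the rule needs correction.

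**What to change.** 1. In the abstract and the Power calculation section, replace the general 95% sentence. State that 5% two-sided is the overall level, that safety non-inferiority is decided by the upper limit of the 95.7% CI against 1.5 points, and that efficacy non-inferiority is decided by the 99.3% CI against 1.5 points.
2. State whether the 0.007 covers one pooled efficacy test or is shared between the balloon and misoprostol tests.
3. In Data analyses, report the two primary risk differences with these deciding intervals, and keep 95% CIs for all other outcomes.
4. Carry the same rule into the SAP, which is still to be finalised before data lock.

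**Cost.** Wording only, with no additional women and no change to 8,891. Any change to the study protocol itself needs the ethics and regulatory approvals described under Study monitoring and safety. Adding alpha recycling would be a separate, optional change to the decision rule in a trial that had already randomised 2,172 women by 10 July 2025. It is not needed to correct this point.

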### Study monitoring and safety

The study is monitored by a professional monitor and a data safety monitoring board (DSMB) including experts in the fields of obstetrics, midwifery, paediatrics and statistics. The DSMB is independent from the sponsor and steering group, and DSMB members have no competing interests. The roles of the monitor and DSMB are defined in the study protocol, monitor contract and DSMB charter.

The monitor ensures that the study is carried out according to the protocol and that data are collected, documented and reported according to International Council for Harmonisation – Good Clinical Practice (ICH-GCP) and applicable ethical and regulatory requirements. Study sites are/will be monitored before the start of recruitment, during the study and after the study as specified in the study’s monitoring plan.

Principally, all components of the primary safety outcome classify as adverse events (AE) or serious adverse events (SAE). As the coordinating principal investigator and the steering group should remain blinded throughout the study, the responsibility for collecting, follow-up, classification and reporting of AE, SAE and suspected unexpected serious adverse reactions (SUSAR) has been delegated to the DSMB in accordance with the Swedish Ethical Review Authority, Swedish Medical Products Agency as well as European Medicines Agency approval. AE, SAE and SUSAR are reported by study staff directly in the eCRF. The DSMB will inform the sponsor in case they judge that reported AE, SAE or SUSAR affect the safety of the study participants. The sponsor representative, steering group and DSMB have at least one meeting every 6 months.

Three interim safety analyses have been prespecified. The first safety analysis after the first 1000 randomised women had given birth did not prompt any changes in the study protocol. Further analyses are planned after 3500 and 6000 randomised women have given birth. Patient groups that are studied in subanalyses during the safety analyses are primiparous and multiparous women, women induced due to PROM or other indications, and women induced primarily with balloon catheter or oral misoprostol. Results are only available for the DSMB; whereas, the sponsor, steering group and statistician remain blinded. According to the DSMB charter, due to the non-inferiority design, the study should not be stopped due to a positive difference in the primary composite endpoint and neither for futility (conditional power). The main aim is to assess safety for the women and foetuses/children involved in the study. If deemed necessary, the DSMB will make recommendations to the sponsor and steering group regarding continuation, modification or termination of any or all arms of the study. All changes to the study protocol and conduction of the study must be approved by the Swedish Ethical Review Authority, the Swedish Medical Products Agency (medical technical device) and the European Medicines Agency (investigational medical product).

Study participants are covered by the Swedish Patient Injury Act and the Pharmaceutical Insurance provided by the healthcare regions.

### Data collection, management, and analysis

#### Data collection

Data will be collected from Swedish quality and mandatory health registers, the study eCRF and questionnaires. Data from the different sources will be linked through the Swedish personal identification number before being replaced by a study ID. Register data will be collected from SPR,^26^ the Swedish Neonatal Quality Register (SNQ),^44^ the Swedish Ambulance Register,^45^ registers at the National Board of Health and Welfare (National Patient Register, the Cause of Death Register, the Prescribed Drug Register)^46^ and Statistics Sweden (SCB),^47^ see table 2. All registers have close to full coverage due to electronic data transfer from hospital charts.

For data collection in the questionnaire and interview part of the study, please see above.

#### Data management

Study-related information will be stored securely in locked file cabinets in areas with limited access at each study site as well as in the study’s eCRF. The eCRF is secured with the hospital staffs’ electronic identification card and a 2-step password-protected access system, and care providers at a certain study site only have access to data from their own site. All electronic data are handled according to the General Data Protection Regulation (GDPR) during collection, analysis and reporting.

#### Data analyses

The final statistical analysis plan (SAP) will be set prior to data lock. All main analyses will be performed according to ITT, and complementary analyses will be performed on the per-protocol population. The statistician performing the analyses will be blinded to allocation and primary IOL method.

For comparison between the two allocation groups, Fisher’s exact test will be used for dichotomous variables, Fisher’s non-parametric permutation test for continuous variables, Mantel-Haenszel χ² test for ordered categorical variables and Pearson’s χ² test for non-ordered categorical variables. For all comparisons between the two groups, regarding dichotomous and continuous variables, mean differences with 95% CI will be calculated.

For the primary outcome variable and other dichotomous outcome variables, multivariable binary regression will be used for the adjustment. For continuous variables, analysis of covariance (ANCOVA) will be used for the adjustment.

For dichotomous variables, risk difference with 95% CI and risk ratio with 95% CI will be calculated between the two groups and 95% CIs for the estimated proportions. The distribution of continuous variables as well as change in continuous variables will be given as mean, SD, median, minimum, maximum, and first and third quartiles. Categorical variables will be given as number and proportion. Exploratory analyses will be performed on subgroups stratified for parity (primiparous vs multiparous women), initial method of IOL (balloon catheter vs oral misoprostol), Bishop score in women without PROM (<3 versus ≥3), indication for IOL (PROM vs other than PROM) and reported travel time to the hospital (<30 min and ≥30 min).

For the health economy analysis, the primary analysis of effectiveness will be comparable to the composite outcome defined as primary outcome.^48^ If non-inferiority is established in the primary analyses, a simpler cost-minimisation analysis will be conducted, that is, only analysing differences in economic costs (and not in relation to the clinical outcomes). All analyses will focus on differences in means between costs and between clinical outcomes. Since cost data are typically non-normal, sampling uncertainty on differences in costs and cost-effectiveness will be assessed by non-parametric bootstrapping.^48^ Applying a simulation model, cost effectiveness for a longer time horizon will be assessed by extrapolation. To do so, associations between neonatal and maternal morbidity and health outcomes later in life will be estimated based on available epidemiologic literature.

For the qualitative studies, data analysis will be conducted by either phenomenology with a lifeworld approach^49^ or content analysis.^43 50^

